## Abstract

**Introduction:** As both the number of cancer survivors and the length of survival time are increasing, long-term health issues related to cancer and its treatment are becoming more prevalent. Research suggests that exercise can mitigate several negative health consequences in cancer survivors and improve physical function and quality of life. Multi-modal exercise interventions have been proposed as a cornerstone for survivorship care. However, studies evaluating exercise programmes within the Irish population are lacking.

**Purpose:** To evaluate the introduction, implementation and acceptability of a multi-modal exercise rehabilitation programme for deconditioned cancer survivors in a real-world, standard practice setting.

**Methods and analysis:** In this single-arm prospective feasibility study, cancer survivors (n=40) will undergo a 10-week multi-modal exercise programme. The study population will comprise of cancer survivors attending outpatient services in an Irish national cancer centre. Participants will be aged 18 or older and have completed treatment with curative intent. Feasibility will be evaluated in terms of recruitment, adherence and compliance to the programme. Secondary outcomes will examine physical function and quality of life measures. In addition, the acceptability of the programme will be assessed through stakeholder feedback.

**Ethics and dissemination**: Ethical approval through the St. James’s Hospital and Tallaght University Hospital Research and Ethics Committee is currently pending. The study results will be used to optimise the intervention content and may serve as the foundation for a larger definitive trial. Results will be disseminated through peer-review journals, congresses and relevant clinical groups.
**Trial registration**: ClinicalTrials.gov
NCT04026659 (19/07/19)

## Introduction

There are currently more than 150,000 cancer survivors in Ireland, and this number continues to rise (
Department of Health, 2017). Furthermore, with advances in early detection and treatment of cancer in the context of an aging population, by 2020 1 in 2 Irish people will be a cancer survivor (
Department of Health, 2017). Subsequently, as both the number of cancer survivors and the length of survival time are increasing, long-term health complications related to cancer treatment are becoming more prevalent (
Miller **et al**., 2016;
Rowland & Bellizzi, 2014).

Depending on treatment pathways, cancer survivors can face several negative consequences of cancer treatment that include psychological (depression or anxiety, fear of recurrence, cognitive impairment) and/or physical symptoms (pain, peripheral neuropathy, sexual dysfunction, gait and balance deficits, joint mobility issues and lymphoedema) (
Beesley *et al*., 2007;
Caraceni & Portenoy, 1999;
Hendren *et al*., 2005;
Massie, 2004;
Mehnert *et al*., 2009;
Mock *et al*., 2001;
O¢Dell & Stubblefield, 2009;
Quasthoff & Hartung, 2002;
Vardy *et al*., 2007). Numerous systematic reviews demonstrate that exercise can mitigate a number of these factors in cancer survivors and improve quality of life, fatigue, physical function and cardiorespiratory fitness and can optimise functional status, preserving the ability to remain in the workforce and fulfil other life roles (
Courneya & Friedenreich, 1999;
Galvão & Newton, 2005;
McNeely *et al*., 2006).

Despite the robust body of existing literature, the integration and delivery of exercise rehabilitation and survivorship into standard clinical cancer care continues to remain the exception rather than the norm (
Mulcahy *et al*., 2018). Internationally, models of cancer survivorship care have been developing rapidly in recent years, many centring on the provision of exercise rehabilitation programmes across diverse delivery settings (
Oeffinger & McCabe, 2006). However, referral to exercise specialists is not a part of the standard care received by oncology patients in Ireland, with a distinct lack of rehabilitation services available for cancer survivors (
Mulcahy *et al*., 2018). There is a need to investigate the feasibility of delivering exercise-based rehabilitation to patients completing cancer treatment.

The aim of the FIXCAS (The Feasibility of Implementing an eXercise programme for deconditioned CAncer Survivors in a national cancer centre) study is to examine the feasibility of implementing a 10-week multi-modal exercise rehabilitation programme to deconditioned cancer survivors in a National Cancer Centre. The implementation of the programme inform the integration of exercise rehabilitation into survivorship services in Ireland.

## Methods

### Study aim

The overall aim of this work is to examine the feasibility of implementing a 10-week multi-modal exercise programme for cancer survivors. Feasibility will be determined by the following outcomes; recruitment, adherence and retention rates, acceptability of the programme and any adverse events.

Secondary aims are:

To examine the effect of the FIXCAS programme on physical function.To examine the effects of the FIXCAS programme on patient reported outcomes including HRQOL and fatigue.To examine the costs associated with a ten-week exercise intervention in the cancer setting. 

### Study design

This is a single-arm prospective feasibility study for deconditioned cancer survivors in a real-world, standard practice setting. A convenience sample of patients (n=40) attending outpatient oncology services in St James’s Hospital, a National Cancer Centre, will be recruited. This centre does not currently have an exercise-based rehabilitation service for cancer survivors. This study will primarily assess feasibility of the exercise intervention and the data from the pilot trial will be used to inform a sample size calculation for a definitive randomised controlled trial.

### Study population

To be eligible to participate in this study, an individual must provide a signed consent form and meet the following eligibility criteria: 18+ years old, diagnosis of solid tumour, completion of chemotherapy and/or radiotherapy and/or surgery with curative intent within the preceding 12 months. All patients must receive medical clearance from their medical team before participating in the study. Only patients who presented with a self-reported loss of functional capacity, including a loss of physical fitness or muscle tone or a decrease in physical activity levels were considered deconditioned and eligible for participation (
Broderick *et al*., 2013). Individuals with moderate or severe cognitive impairment, currently pregnant or receiving treatment in the palliative setting will be excluded from participation in this study.

### Recruitment

Potential participants will be recruited by direct invitation from study personnel in oncology clinics, by recommendation from medical or multidisciplinary colleagues, or by responding to mail-out of a study leaflet (sent out to individuals consenting to mail-out of information). Informed consent will be obtained in writing from participants by designated members of the research team (Extended data (
[name], 2019)).

### Intervention

The FIXCAS multi-modal exercise programme is designed in accordance with international guidelines for best practice exercise prescription for people with cancer (
Schmitz *et al*., 2010). The FIXCAS exercise programme is theoretically underpinned by the Theory of Planned Behaviour, the most widely used theory of exercise motivation for people with cancer (
Armitage & Conner, 2001;
Rhodes & Courneya, 2003). The intervention consisted of three motivational techniques designed to translate intentions into behavior. Patients set weekly goals for their home-based exercise and also received an exercise information booklet from the research team (instruction on how to perform the behavior). Patients also received feedback on their weekly physical activity from the research team during weekly exercise sessions.

The exercise programme includes 10 weeks of twice weekly group-based exercise sessions administered under the supervision of a physiotherapist with extensive training in the area of oncology. Each exercise session will last approximately 1 hour and consist of a combination of aerobic, resistance and balance and flexibility exercises (
Figure 1).

**Figure 1. f1:**
[figure not shown]
Outline of Exercise Intervention.

***Aerobic exercise*** will consist of 20 to 30 min of moderate intensity cardiovascular exercise using a variety of modalities such as walking or jogging on a treadmill, cycling or rowing on a stationary ergometer. Patient’s baseline activity levels, exercise preferences and physical impairments will inform the choice of exercise modalities. Heart rate will be monitored using Polar FT7 heart rate monitors (Polar Electro, Lake Success, NY) and the BORG Rating of Perceived Exertion (
Borg, 1998). Participants will exercise to a target intensity of 40–70% of estimated heart rate reserve (HRR) or 12–15 on the BORG Rating of Perceived Exertion (RPE) scale. Aerobic exercise will commence at a low intensity (40–55% HRR) and progress to moderate intensity (55–70% HRR) over the 10-week programme.

***Resistance exercise*** will target the large muscle groups of the upper and lower extremities be performed at 40% to 70% of the measured one repetition maximum (1-RM) and consist of two sets of 10–15 repetitions. Resistance exercise will commence at a light to moderate intensity and will progress to a moderate intensity over the 10-week programme. Eight major upper limb and lower limb muscle groups will be exercised eg. biceps curl, leg extension.

***Flexibility and balance exercise*** will be incorporated into the two supervised weekly sessions, as per current guidelines.

***Self-directed care:*** A home exercise programme is included as a self-managed component of the programme which aligns with national recommendations for survivorship care. This self-management component is included to improve compliance and stimulate physical activity outside the exercise programme. Patients will be encouraged to be moderately physically active for at least 30 minutes, three times per week in addition to the supervised programme in order to meet current physical activity guidelines (
Schmitz *et al*., 2010).

***Maintenance of the exercise intervention:*** All patients completing the FIXCAS programme will receive a written exercise summary upon completion (extended data (
[name], 2019)) of the programme to facilitate transition to a local community exercise setting.

### Outcomes

Outcomes will be assessed at baseline (T1) and at the completion of the 10-week intervention (T2). A follow up Quality of Life (QoL) Questionnaire (EQ-5D-5L) will be posted to participants 3 months postintervention (T3).
Table 1 outlines the schedule of study assessments. A member of the research team will collect quantitative measures across all study time points. The qualitative element of the study will be undertaken after completion of the exercise programme.

**Table 1. T1:** Outline of study assessments. EQ-5D-5L: EuroQol-5D-5L; IPAQ: International Physical Activity Questionnaire; SPPB: Short Physical Performance Battery; 1-RM: 1 Repetition Maximum; EORTC-QLQ-C30: European Organisation for Research and Treatment of Cancer- Quality of Life Questionnaire-C30.

Timepoints		Pre-Screening Telephone Call	T1 Pre-intervention	10-week intervention	T2 Post Intervention	T3 3 months post intervention
**Initial Study** **Procedures**	Explain study	X	X			
	Screen eligibility criteria	X	X			
	Sign consent form		X			
	Case report form and clinical data		X			
**Feasibility** **Outcomes**	Enrolment rates		X			
	Adherence			X		
	Adverse Events			X		
	Retention rates			X	X	
	Stakeholder feedback					X
**Secondary Study** **Outcomes**	EQ-5D5L		X		X	X
	Cost analysis of programme					X
	Six-minute walk test		X		X	
	IPAQ		X		X	
	SPPB		X		X	
	1-RM		X		X	
	EORTC-QLQ-C30		X		X	
	Brief Fatigue Inventory		X		X	
	Body composition		X		X	
	International Consultation on Incontinence Questionnaire (Prostate cancer only)		X		X	
	Brief Male Sexual Function Inventory (Prostate cancer only)		X		X	

***Primary outcome.*** The primary outcome of this study will be its feasibility aspects, including recruitment rates (percentage of eligible study population that consented to participation), programme adherence (number of prescribed supervised and unsupervised sessions completed), retention, acceptability of the intervention and adverse events. Reasons for poor enrolment, attrition or non-compliance will be identified through qualitative evaluation with participants and medical professionals upon programme completion.

***Secondary outcomes.*** Several secondary outcomes will investigate the impact of the intervention on physical function and QoL. Physical fitness will be measured by the 6 minute walk test (6MWT), a valid and reliable measure of physical fitness in people with cancer which will be performed according to the American Thoracic Society (ATS) Guidelines (
American Thoracic Society, 2002;
Schmidt *et al*., 2013). Self-reported physical activity will be collected using the International Physical Activity Questionnaire (IPAQ) (
Hagströmer *et al*., 2006). Physical Performance will be measured by a Short Physical Performance Battery (SPPB) and a lower limb strength test (Leg extension 1-Repitition Max).

Quality of life is evaluated through the internationally established European Organisation for the Research and Treatment of Cancer Core Quality of Life Questionnaire (EORTC-QLQ-C30) (
Aaronson *et al*., 1993). It assesses important functioning domains (e.g. physical, emotional, role) and common cancer symptoms (e.g. fatigue, pain, nausea/vomiting, appetite loss) (
Aaronson *et al*., 1993). Euro-QoL (EQ-5D5L) a generic quality of life measure will also be used (
Herdman *et al*., 2011). This measure will be completed by all participants and will form part of the cost analysis of the programme. Fatigue will be assessed using the Brief Fatigue Inventory (BFI) (
Mendoza *et al*., 1999). Prostate cancer survivors will complete questionnaires on incontinence (International Consultation on Incontinence Questionnaire) (
Hajebrahimi *et al*., 2004) and sexual function (Brief Male Sexual Function Inventory) (
O¢Leary *et al*., 1995). Both incontinence and sexual function may be affected by the exercise intervention (
Baumann *et al*., 2012).

A needs assessment (impairment screening) of each individual will be collected at T1 and T2 study assessments. Body composition will also be collected at T1 and T2. Weight (kilogrammes (kg)) and height (centimetres (cm)) will be recorded by standard methods and body mass index (BMI) will be calculated as weight (kg)/ height (metres (m
^2^)). Adverse outcomes will be recorded throughout the study period.

***Qualitative evaluation.*** Acceptability of the intervention will be explored through qualitative interviews. Key stakeholders, namely participants in the exercise intervention and health professionals referring to the exercise programme, chosen at random, will be invited to participate in semi-structured feedback interviews. Open-ended questions will be used to encourage open dialogue and elaboration on different aspects of the programme. Health professionals (n=8-10) referring to the programme will be interviewed to examine their experience of referring to the FIXCAS programme to identify barriers and facilitators to referral and to determine areas for review and further development. Patients (n=10-15) will be asked to evaluate satisfaction with the intervention. The interviews will be audio recorded and transcribed, following which data analysis of the interviews will occur through content analysis using simple descriptive thematic analyses.

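### Reasons for poor enrolment and barriers to referral are sought from an interview frame that leaves out patients who declined and clinicians who did not refer

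*Protocol article*

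**What the plan says.** The Primary outcome paragraph of the protocol article lists recruitment, adherence, retention, acceptability and adverse events as the feasibility outcomes. Recruitment is defined as the share of eligible patients who give consent. The paragraph then names where explanations will come from: "Reasons for poor enrolment, attrition or non-compliance will be identified through qualitative evaluation with participants and medical professionals upon programme completion".

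The Qualitative evaluation paragraph fixes who can be interviewed: "namely participants in the exercise intervention and health professionals referring to the exercise programme, chosen at random, will be invited". For clinicians it adds: "Health professionals (n=8-10) referring to the programme will be interviewed to examine their experience of referring to the FIXCAS programme", with the purpose "to identify barriers and facilitators to referral and to determine areas for review and further development". For patients it gives a target of 10-15 and describes the topic only as satisfaction with the programme.

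On timing, the opening of Outcomes says: "The qualitative element of the study will be undertaken after completion of the exercise programme". Table 1 marks "Stakeholder feedback" at T3 only, three months after the intervention.

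The Safety section invites people who withdraw to attend assessment. It mentions neither an interview nor a recorded reason for leaving.

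**The concern.** Why eligible patients did not enrol is best answered by patients who did not enrol. Why clinicians did not refer is best answered by clinicians who did not refer. The protocol states both questions, then fixes a sampling frame that contains neither group. This does not depend on what the article leaves out: the method, the two source groups and the random selection are all written down.

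If enrolment is low, the study will report a recruitment rate without a first-hand account of why it was low. The results are meant to optimise the programme and may be the foundation for a larger trial (Ethics and dissemination; Conclusion). A planner would need to know whether refusals came from travel, timing, lack of interest or something else, and whether some clinics never offered the programme.

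Drop-outs raise a lesser question. They may be in the frame, but nothing ensures that enough of them are heard to explain attrition.

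**Working it through.** The protocol gives no calculated figure to reproduce. The sample of 40 has no calculation behind it (Sample size and statistical analysis), and the interview numbers are plain targets.

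**Step 1: compare each stated question with the people who can be interviewed.**

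| Question the protocol poses | Group with first-hand knowledge | In the frame? |
|---|---|---|
| Reasons for poor enrolment | Eligible patients who declined | No |
| Barriers to referral | Clinicians who referred few or none | Low referrers yes; non-referrers no |
| Reasons for attrition | Drop-outs | Not excluded; selected by chance |
| Reasons for non-compliance | Low attenders | Yes; selected by chance |

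The number of decliners and of non-referrers interviewed is 0 by definition of the frame. This needs no assumption.

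**Step 2: how many decliners might there be?** The consent rate r is not given, so it is assumed. With 40 consenting, decliners = 40/r − 40.

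- r = 70%: 57.1 − 40 = about 17
- r = 50%: 80 − 40 = 40
- r = 30%: 133.3 − 40 = about 93

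**Step 3: how many drop-outs would random selection bring in?** Inputs: 40 enrolled and n = 10 to 15 patient interviews, both from the protocol; D drop-outs, assumed because no rate is given. Random selection is taken to cover all 40, including those who left. The count is then hypergeometric, with expected number = n × D/40 and P(none) = C(40 − D, n)/C(40, n).

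| Assumed drop-out | D | Expected, n = 10 | Expected, n = 15 | P(none), n = 10 | P(none), n = 15 |
|---|---|---|---|---|---|
| 5% | 2 | 0.5 | 0.75 | 0.56 | 0.39 |
| 10% | 4 | 1.0 | 1.5 | 0.30 | 0.14 |
| 20% | 8 | 2.0 | 3.0 | 0.08 | 0.01 |
| 30% | 12 | 3.0 | 4.5 | 0.015 | 0.001 |
| 40% | 16 | 4.0 | 6.0 | 0.002 | below 0.001 |

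Worked case: D = 4, n = 10 gives (30 × 29 × 28 × 27)/(40 × 39 × 38 × 37) = 657,720/2,193,360 = 0.30.

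These figures assume that everyone selected agrees to an interview. If only completers were interviewed, the number of drop-outs would be 0, but the text does not say that.

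**The case against.** The strongest reply is that the frame is less empty than it looks.

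- **Clinicians can report refusals.** The enrolment sentence names medical professionals, and those who raise the programme with patients will often hear why some say no. This stands: second-hand information is possible, so it would be too strong to say that reasons for poor enrolment cannot be found at all. It is weaker evidence, however, and the Recruitment section also allows direct invitation by study staff and a mailed leaflet, where there may be no referrer to ask.
- **Referrers know about barriers.** A clinician may refer some patients and not others, and can describe what got in the way. This also stands. What is lost is the view of those whom the barriers stopped altogether.
- **Drop-outs are represented.** A reader might infer that the patient interviews are tilted towards satisfied completers and so overstate acceptability. The text does not support this. Selection is from participants, not completers, and a random draw includes drop-outs in proportion. Only unequal willingness to be interviewed could create a tilt; it cannot be sized from the protocol and would affect a purposive sample too. With 8 drop-outs in 40 and 12 interviews, P(none) is 0.040, so the chance of hearing at least one is 96%.
- **Timing.** A reader might also see a contradiction between interviews at programme completion and Table 1's T3. T3 is still after completion, which is what the opening of Outcomes requires. Only a strict reading of the word upon clashes with it, so this is a matter of alignment.
- **The forms may hold reasons.** The case report form is listed under Extended data and is not shown; it may have a field for reasons. Absence of such a field is therefore not claimed. The point rests on the protocol naming the interviews as the source.

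**Conclusion.** The point holds in a limited form: the stated aim is wider than the interview frame set to serve it. Followed as written, the plan hears no decliner and no non-referring clinician first-hand, whatever the consent or drop-out rate. Reasons for poor enrolment would be second-hand, and barriers to referral would come only from people who did refer.

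The drop-out part is conditional. At an assumed 10-20% drop-out, 1 to 3 are expected among 10-15 interviews, which is thin for explaining attrition. At 30-40% the expected number is 3 to 6 and the worry weakens. Low attenders who remain in the study are in the frame, so non-compliance can be explored, though only as far as the random draw allows.

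The feasibility rates themselves are unaffected. What suffers is the ability to explain them. The change is worth making because those explanations are what a larger trial would build on.

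**What to change.** 1. **Keep the interview numbers but sample purposively.** Reserve some of the 10-15 patient interviews for drop-outs, low attenders and decliners who are willing to talk, and some of the 8-10 clinician interviews for eligible clinic staff who referred few or no patients. For example, about 5 patient and 3 clinician places would leave 5-10 and 5-7 for the rest. The split is a judgement, not a derived figure. Rewrite the Qualitative evaluation paragraph so that these groups are in the frame, and widen the patient topic beyond satisfaction.
2. **Name a second source of reasons.** State that an optional one-line reason at decline and at withdrawal will be used, adding the fields only if the existing forms lack them.
3. **If neither is wanted, narrow the aim** to the views of participants and referrers on enrolment, attrition and referral.
4. **Minor:** align the timing phrase in the Primary outcome paragraph with the T3 entry in Table 1.

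The cost is no extra interviews, a small change to the ethics application to cover inviting decliners and people who withdraw, and slightly fewer interviews with typical completers. Reserved places also give up proportional representation, so the report should describe views by group and not present them as those of the average participant. The Study status section says that approval was pending and recruitment had not begun, so at that stage the change was cheap.
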